**Fig. 4 Fig4:**
[figure not shown]
Composite Outcome Classification Algorithm. *Figure Legend*: The gold standard composite diagnostic algorithm comprises symptoms, CXR findings, GeneXpert® Ultra, TB microscopy, TB culture results and treatment response

#### Data management and statistics

Data will be entered directly or from paper-source into electronic format using Research Electronic Data Capture (REDCap®). Quality control will include two-step data verification of all forms of data using REDCap® in-built QC capability. The database will also undergo regular central monitoring of key fields by the Sponsor to ensure completeness and accuracy. Classification into gold standard TB Outcome groups will be automated and verified by the attending clinician. Data analysis will be performed by the Stellenbosch University Bioinformatics unit. Basic descriptive statistics will be used to describe the study population. All estimates will be reported with 95% confidence intervals (CI). The main outcomes of interest are the sensitivity, specificity, positive and negative predictive values of the MBT, biomarkers and biosignatures, and algorithmic combinations to differentiate *Definite* and *Probable TB* from *No TB*. These will be analysed using Receiver Operating Characteristic (ROC) curves with Area Under Curve (AUC). There will be a direct comparison of biomarker quantification using the 3-marker MBT and Luminex in Phase 1, determining the reproducibility of the laboratory-based tests and POC tests, using the Kappa statistic for agreement, as well as the performance of the tests in different countries and sub-populations such as those with HIV, previous TB episodes and smear-negative TB. To arrive at the global diagnostic signature, predictive algorithms will be developed using machine learning methods and tested for out-of-sample performance. These will be adapted if the bio-signature requires amendment.

Sample size calculations are for the validation of the MBT in Phase 2, required endpoints being sensitivity, specificity, positive and negative predictive value with 95% CI, with half-width dependent on sample size. For Phase 2, 80 participants (one-third of the 250 per site) are expected to have active TB from previous trial experience, resulting in a target sensitivity of 90% with a 95% CI half-width of 5%. Thus, target precision should be achieved for analysis of MBT performance at each site and overall.

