## Background

Pulmonary tuberculosis (PTB) is still a leading cause of death and places severe pressure on health care systems of low- and middle-income countries [1]. The number of TB cases is not dropping fast enough to reach the 2030 End TB Strategy milestones and the COVID-19 pandemic has further slowed progress [1, 2]. Each year, 3.6 million people with TB still go undiagnosed, and approximately 30% of patients diagnosed with TB are not treated [2]. The high burden of undiagnosed and untreated TB further fuels ongoing transmission [1–3].

TB testing remains costly, imperfect, and of limited accessibility even in high TB prevalence areas. The highly sensitive and specific GeneXpert® MTB/RIF or Ultra (GeneXpert®) [4] has shown great promise for rapid detection of active TB, but the cost is high. Furthermore, GeneXpert® is in practice frequently a central laboratory-based platform rather than point-of-care (POC), and is subject to logistical challenges and loss to follow-up [5]. Liquid culture is even less accessible than GeneXpert®, prone to contamination, and takes 42 days for a negative result [6]. Traditional chest X-rays (CXR) are also unsuitable as rapid diagnostic or screening tools. They are relatively expensive, non-specific and at present, depend on skilled personnel for interpretation.

Active pulmonary TB will only be confirmed in approximately one-third of those that undergo costly and time-consuming testing for TB based on suggestive respiratory symptoms [7]. This represents an inefficient use of sparse and expensive resources. Focussing TB investigation could streamline resource use, thereby improving TB care in overburdened health care systems [8]. The World Health Organisation (WHO) has re-emphasised the need for efficient TB screening and seeks a non-sputum based screening tool to narrow TB testing to those patients with a high likelihood of PTB [8]. Such a test should be appropriate for global use and have comparable validity to the WHO minimum target product profile (TPP) sensitivity of 90% and specificity of 70% [8].

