Specific host biomarkers (human proteins and RNA) have been linked with active TB disease [9–16]. These represent attractive targets for integration into non-sputum-based triage tests [8]. Over a series of previous EDCTP-funded studies since 2010, the Triage Consortium have discovered protein biomarkers present in the blood and associated with a high likelihood of active TB disease [7, 11, 17–19]. These have been progressively narrowed to a signature consisting of three biomarkers (CRP, SAA and IP-10). This signature has been preliminarily validated using samples from African people with TB symptoms (unpublished). Further testing is required to see if this signature would achieve global applicability. As it was validated using serum, this signature also needs further evaluation of its validity on fingerstick blood. A further 10–15 protein biomarkers showed promise for the purpose of triaging symptomatic patients, and further analysis of these is needed to yield the smallest, most practical signature [7, 17].

Subsequent to previous EDCTP-funded studies (AE-TBC and Screen-TB), we advance a prototype lateral flow (LF) based quantitative diagnostic to a point-of-care (POC) applicable test to measure multiple TB-associated host protein biomarkers in fingerstick blood [7, 20, 21]. This multi-biomarker test (MBT) assay comprises a single LF-based test device which measures individual concentrations of multiple biomarkers, using a luminescent label [up-converting reporter particle (UCP) technology] for quantitation. MBT results can be assessed on a battery-powered stand-alone portable reader to yield immediate results. The test format is highly flexible in the number and identity of biomarkers that can be analysed. The UCP label is not hampered by the red colour produced by haemolysis of erythrocytes, allowing convenient dilution of collected fingerstick blood using a lysis buffer. In comparison to other fluorescent labels, the UCP reporter is not light sensitive, does not fade and has an infinite lifetime. The device has been tested in a laboratory environment but has had limited field testing.

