**Fig. 1 Fig1:**
[figure not shown]
Schematic of study design

During Phase 1a, sensitivity and specificity for active TB will be determined for serum biomarkers (CRP, IP-10, SAA, ferritin and 10–15 other promising candidate biomarkers) using 500 stored serum samples obtained through FIND from diagnostic studies in South Africa, Vietnam and Peru using Luminex and Meso Scale Diagnostics (MSD). Phase 1b will validate the MBT among 50 participants per site (total 200), prior to lockdown of applied host biomarkers and test format. Following Phase 1 will be a break in enrolment for analysis and derivation of a global diagnostic biomarker signature to be incorporated into the MBT for Phase 2. Phase 2 will validate the MBT with the final signature among 250 participants per site (total 1000).

The two consecutive phases of the validation study follow the same study schedule. A cross-sectional validation of the POC diagnostics will be followed by a longitudinal evaluation of participants diagnosed with TB, to evaluate the tests’ ability to monitor treatment response and predict cure at the end of treatment. Samples, data and chest X-ray’s from both phases will be stored at the sponsor site’s biorepository and central server respectively to allow for later evaluation of future candidate tests.

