### MBT format

Figure 2 displays various available MBT formats. The MBT device can hold various sized lateral flow strips, on which each test line detects and quantifies a unique biomarker. One or more standard-sized strips, each with up to three test lines, or one non-standard-sized strip with width determined by the number of parallel slanted test lines, can be used. Standard size would be preferred when considering low cost production utilizing existing production lines from external manufacturers. The ESEQuant LR3 reader (DIALUNOX GmbH, Stockach, Germany) allows for 2D scanning, which has enabled the parallel MBT format. The use of parallel strips, each specific for a single biomarker, minimizes potential cross reactivity. Available standard cassettes can hold 3 parallel strips with standard dimensions, important for industrial production. In phase 1a of the Triage-TB study, performance of the three markers in the Triage Consortium biosignature will be evaluated on a global cohort, using 3-marker MBT strip formats better suited for potential future production. In Phase 1b of Triage-TB, performance of the MBT on fingerstick blood (FSB) will be evaluated and compared to serum. In addition, lysed FSB will be compared to whole FSB. Testing strips for the whole FSB will be provided in a cassette and run horizontally immediately after sampling. Strips for the lysed FSB and serum testing will be provided with microtiter plates to run vertically in the laboratory. A schematic for the approach followed in phase 1B is shown in Fig. 3. For phase 2 of Triage-TB, the chosen MBT format will need to be suitable for industrialisation and for the implementation of the best performing marker combination.

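### Kappa is the only agreement statistic named for comparing MBT and Luminex concentrations, and it cannot measure bias between the platforms or separate it from random error

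*Protocol article*

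**What the plan says.** All places are in the protocol article.

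- **Data management and statistics**, on the comparison: "There will be a direct comparison of biomarker quantification using the 3-marker MBT and Luminex in Phase 1". The sentence continues with the method: "determining the reproducibility of the laboratory-based tests and POC tests, using the Kappa statistic for agreement". It gives no categories, weights or cut-off for kappa, and no method for agreement on a continuous scale.
- **Background**, on the MBT: it is a device "which measures individual concentrations of multiple biomarkers".
- **MBT format**, on the strips: "on which each test line detects and quantifies a unique biomarker".
- **Study design** (text under Fig. 1), on the use of Phase 1: a pause in enrolment for analysis and "derivation of a global diagnostic biomarker signature to be incorporated into the MBT for Phase 2".

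The other analysis named for marker readings is ROC/AUC against the composite reference standard. AUC depends on ranks only, so a constant proportional difference between platforms leaves each marker's AUC unchanged. It therefore does not supply what the agreement analysis lacks.

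**The concern.** A comparison of quantification asks two things: whether one platform reads systematically higher or lower than the other, and how far apart individual paired readings lie. Kappa answers neither. It is undefined on concentrations until they are cut into classes. After that it records only whether two readings fall in the same class, and its value depends on the cut and on the share of participants above it.

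The article does not leave the method open. It names one, and that one does not fit the stated comparison. Phase 1 feeds the decision on what goes into the Phase 2 device, so a reader of the Phase 1 report would want to know whether MBT and Luminex readings of CRP, IP-10 and SAA are interchangeable, and if not, by what factor they differ. Kappa alone could look reassuring when they differ by a constant factor, or look poor without showing why.

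**Working it through.** The article gives no expected kappa, bias or limits of agreement, so there is no figure to reproduce. The check is of the mechanism.

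**Inputs from the article.** TB prevalence about one third ("one-third of the 250 per site"), and a cut-off placed at the 90% sensitivity / 70% specificity target in Background.

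**Assumptions, not from the article.** One log-normal marker, log-SD 1 within each group, log-means 1.25 (TB) and -0.6 (no TB). MBT = f × Luminex, with independent log-scale noise of SD 0, 0.2 or 0.4 on each platform.

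**1. Kappa under proportional bias.** Simulation with N = 400,000 and the cut-off at 90% sensitivity:

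| f | noise SD | kappa, own cut-offs | kappa, common cut-off | geometric mean ratio | concordance (log) |
|---|---|---|---|---|---|
| 1 | 0 | 1.00 | 1.00 | 1.00 | 1.00 |
| 1.5 | 0 | 1.00 | 0.76 | 1.50 | 0.96 |
| 2 | 0 | 1.00 | 0.60 | 2.00 | 0.88 |
| 3 | 0 | 1.00 | 0.39 | 3.00 | 0.75 |
| 1 | 0.2 | 0.87 | 0.87 | 1.00 | 0.98 |
| 2 | 0.2 | 0.87 | 0.60 | 2.00 | 0.86 |
| 1 | 0.4 | 0.75 | 0.75 | 1.00 | 0.92 |
| 2 | 0.4 | 0.75 | 0.58 | 2.00 | 0.81 |

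With own cut-offs kappa does not respond to f. With a common cut-off it does.

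Hand check of the common cut-off at f = 2 without noise. The cut is 1.25 - 1.2816 = -0.032. Luminex calls 49.0% positive and MBT 69.2%. Every Luminex positive is also MBT positive, so observed agreement is 1 - (0.692 - 0.490) = 0.798. Chance agreement is 0.490 × 0.692 + 0.510 × 0.308 = 0.496. Kappa = (0.798 - 0.496)/(1 - 0.496) = 0.60.

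**2. One kappa, two causes.** With f = 1 (no bias) and noise SD 0.65 on each platform, the common-cut-off kappa is also 0.60. Ratio limits of agreement, f × exp(±1.96 × SD × √2), separate the cases:

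- f = 2, no noise: mean ratio 2.00, limits 2.00 to 2.00.
- f = 2, SD 0.2: 1.96 × 0.2 × 1.414 = 0.554, so mean ratio 2.00, limits 1.15 to 3.48.
- f = 1, SD 0.65: 1.96 × 0.65 × 1.414 = 1.802, so mean ratio 1.00, limits 0.17 to 6.06.

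Kappa is 0.60 in all three.

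**3. A second set of assumptions, in closed form.** Bivariate normal log readings with correlation 0.9 and SD 1. At own-median cuts kappa = (2/π) × arcsin(0.9) = 0.71, whatever f is. Concordance = 1.8/(2 + (ln f)²), which is 0.90 at f = 1, 0.73 at f = 2 and 0.56 at f = 3. Moving both cuts from the median to the 10th or 90th percentile changes kappa from 0.71 to 0.65 on the same data, a modest effect.

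**4. Conditional effect on accuracy.** Suppose a Luminex cut-off were applied unchanged to MBT readings of one normally distributed log marker. For 90%/70% the cut is 0.524 above the no-TB mean and the group separation is 0.524 + 1.282 = 1.806. Sensitivity = Φ(1.282 + ln f) and specificity = Φ(0.524 - ln f).

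- f = 0.5: Φ(0.588) = 72% and Φ(1.217) = 89%.
- f = 2: Φ(1.975) = 98% and Φ(-0.169) = 43%.

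The simulation at noise SD 0.2 gives 72.5%/89% and 97.5%/44%.

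**The case against.** The strongest reply is that kappa may be meant for positive/negative calls, since its clause speaks of the reproducibility of laboratory and POC tests. Kappa is conventional for that, and a condensed article need not give cut-offs or weights. The sentence does allow this reading. But the clause hangs on a comparison of quantification, and under this reading that comparison has no method. Read literally, it has the wrong one. Either way it is worth saying what kappa is applied to.

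Three stronger conclusions are tempting, and the article does not support them.

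- **That kappa cannot detect proportional bias.** This is true only with platform-specific cut-offs or quantiles. With a common cut-off kappa falls, as the table shows. The article does not say which would be used.
- **That the choice of kappa would shift the test's cut-off and lose the 90%/70% target.** Nothing in the article says a Luminex cut-off is carried to the MBT. Objectives and MBT format put the MBT itself on stored serum in Phase 1a and on fingerstick blood in Phase 1b, before lockdown. A cut-off set on those readings would absorb a constant proportional bias. Phase 2 then validates the locked device directly in 1000 participants, where a misplaced cut-off would show.
- **That kappa also governs serum versus fingerstick and lysed versus whole blood.** Those comparisons are described under MBT format, where kappa is not named.

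It is also fair that the fold biases, correlation and noise are assumed, and that the planned signature combines several markers by machine learning, so the single-marker accuracy figures are illustrations only.

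**Conclusion.** The point holds in limited form. The only agreement statistic named for a comparison of concentrations is a categorical one. It cannot estimate proportional bias or distinguish it from random error, and it misses such bias altogether when each platform has its own cut-off. Under the stated assumptions, a two-fold bias leaves own-cut-off kappa unchanged (1.00, 0.87 or 0.75 by noise level). Common-cut-off kappa falls to about 0.6, a value that unbiased noise can also produce.

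The shifts to 72%/89% or 98%/43% are not predictions for this study. They require a single marker, a two-fold difference and transfer of a Luminex cut-off to the MBT, and the article states none of the three. The comparison is a supporting Phase 1 analysis. The main outcomes (sensitivity, specificity and predictive values) do not depend on kappa.

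**What to change.** Replace the kappa clause in Data management and statistics with a method on the measured scale. For each of the three markers, compare paired MBT and Luminex readings on log concentrations and report the mean ratio with 95% limits of agreement, and the Deming or Passing-Bablok slope and intercept with 95% CIs. Keep kappa, with overall percent agreement, only for the dichotomised test result, and state the cut-off and whether it is common to both platforms.

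The cost is one sentence of text and a little more analysis of the same data. It needs no new samples or participants.

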### Gold standard classification

The POC investigational assays will be measured against a composite diagnostic algorithm comprising symptoms, chest Xray findings, sputum GeneXpert® Ultra, TB microscopy, TB culture results, and treatment response (Fig. 4). Potential outcomes are *Definite TB, Probable TB, Possible TB,* and *No TB.* Participants classified as Definite TB or Probable TB will be regarded as gold standard *positive,* and participants with No TB will be regarded as gold standard *negative*. *Definite TB* denotes sputum culture or GeneXpert® Ultra confirmation; *Probable TB* is a combination of radiological or microbiological evidence with a good response to treatment; and *No TB* indicates that all tests are negative for TB and that an alternative diagnosis exists. *Possible TB* occurs in cases with contradicting evidence, often due to loss to follow-up. This category is excluded from analysis because of the uncertainty of TB disease.

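### Eighty TB cases per site give a 95% CI half-width of about 6.6 points at 90% sensitivity, not 5, so the stated precision holds overall but not at each site

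*Protocol article*

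**What the plan says.** The Protocol article gives its sample-size reasoning in the last paragraph of Data management and statistics. It concerns validation of the MBT in Phase 2. The required endpoints are sensitivity, specificity and the two predictive values with 95% confidence intervals, and their half-widths are said to depend on sample size.

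The only worked figure is for sensitivity. The paragraph states that "80 participants (one-third of the 250 per site) are expected to have active TB", citing earlier trial experience, "resulting in a target sensitivity of 90% with a 95% CI half-width of 5" per cent. It concludes: "Thus, target precision should be achieved for analysis of MBT performance at each site and overall".

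Two other places bear on the point. The text with Fig. 1 sets Phase 2 at 250 participants at each of four sites, 1000 in all. Gold standard classification counts Definite and Probable TB as positive and No TB as negative. Of Possible TB it says: "This category is excluded from analysis because of the uncertainty of TB disease".

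**The concern.** The paragraph gives a number of cases, an assumed sensitivity and a confidence level, and together these fix the half-width. The stated 5% is too small for 80 cases at 90%. It is not the pooled figure either, because the 80 is tied to the 250 at one site and the conclusion names the sites separately.

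This is the only sample-size justification shown. The same section plans to examine performance in different countries, and the benchmark in the Background is the WHO minimum of 90% sensitivity and 70% specificity. The Discussion describes the goal as a rule-out test, for which the lower confidence limit of sensitivity matters most. A reader who trusts the paragraph would expect a site observing 90% to have a lower limit near 85%. The design does not provide that.

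**Working it through.** **Inputs, all from the Protocol article**
- Confidence level: 95%, two-sided (Data management and statistics).
- TB cases per site: 80, described as one-third of 250 (same section). Exactly one-third is 83.3.
- Sensitivity: 90%; stated half-width: 5 points (same section).
- Sites: four, 250 participants each (text with Fig. 1).

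**Step 1. Try to reproduce the stated 5 points at one site.** The Wald half-width is 1.96 × √(p(1−p)/n).
- n = 80, p = 0.90: 1.96 × √(0.09/80) = 1.96 × 0.0335 = 0.0657, or 6.6 points. The stated figure is not reproduced.

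**Step 2. Try other two-sided 95% methods for 72/80.**

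| Method | Interval | Half-width (points) |
|---|---|---|
| Wald | 83.4% to 96.6% | 6.57 |
| Jeffreys | 82.0% to 95.2% | 6.57 |
| Wilson | 81.5% to 94.8% | 6.68 |
| Agresti–Coull | 81.3% to 95.1% | 6.91 |
| Clopper–Pearson | 81.2% to 95.6% | 7.17 |

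The upper arm of the Wilson interval is 4.85 points, but its lower arm is 8.5 points, so this is not a half-width of 5.

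**Step 3. Try more favourable readings (Wald).**
- 83 or 84 cases instead of 80: 6.45 or 6.42 points.
- z = 1.645 (a 90% interval, or one-sided 95%): 5.52 points.
- Finite-population correction, 80 of 250: 6.57 × √(170/249) = 5.43 points.
- Sensitivity that would give 5 points with 80 cases: p(1−p) = 80 × (0.05/1.96)² = 0.0521, so p is about 94.5%, not 90%.

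None of these gives 5 points at 90% sensitivity.

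**Step 4. Cases needed for 5 points at 90%.**
- n = 1.96² × 0.09/0.05² = 138.3, so 139 TB cases per site.
- That is 139 × 3 = 417 participants per site at one-third prevalence, or 139/0.32 = 435 (rounded up) at 80 in 250. The plan has 250.

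**Step 5. The overall claim.**
- 4 × 80 = 320 cases: 1.96 × √(0.09/320) = 0.0329, or 3.3 points.
- 333 cases (one-third of 1000): 3.2 points.

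Both are within 5 points.

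**Step 6. For information only.**
- Specificity at 70%, with at most 250 − 80 = 170 non-TB participants per site: 1.96 × √(0.21/170) = 6.9 points. With at most 680 overall: 3.4 points.
- If 10% of the 80 cases were lost to the Possible TB category (an assumed share): 72 cases give 1.96 × √(0.09/72) = 6.9 points.

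**The case against.** The strongest reply is that the practical damage is small. On the same Wald scale, the site-level lower limit at an observed 90% is 83.4% against the implied 85%, a gap of 1.6 points. The text shows no site-level hypothesis test or pass/fail rule, so no decision is shown to change, and the pooled estimate meets the target comfortably. All of this is right. It limits the consequence but does not rescue the figure.

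A reader might also infer more than the document supports:

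- **That specificity and the predictive values miss a 5-point target too.** The text attaches 5% to sensitivity alone and otherwise says only that half-widths depend on sample size. The closing reference to MBT performance is ambiguous at most. A site specificity half-width of 6.9 points is useful to know but is not a missed target.
- **That the 80 is counted before Possible TB is removed.** The paragraph does not say. The 80 is described as those expected to have active TB, it is slightly below one-third of 250, and it may already mean Definite plus Probable TB. This is an open question.
- **That a site with lower prevalence would do much worse.** It would have wider intervals, but the document gives no prevalence other than about one-third.
- **That site results must be downgraded to supportive.** That would be a choice about inferential standing. The arithmetic does not require it.

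A fuller protocol or an analysis plan could settle some of these points. It could not make 80 cases yield 5 points at 90%.

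**Conclusion.** The site-level precision statement is wrong as written. At 90% sensitivity, 80 TB cases give a 95% half-width of about 6.6 points (6.6 to 7.2 across standard methods) instead of 5, and 5 points would need about 139 cases per site. The claim for the pooled analysis is right, at about 3.3 points with 320 cases.

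This rests on the document's own 80 cases per site and 90% sensitivity, and on treating each estimate as a simple binomial proportion, including the pooled one. It does not depend on how Possible TB is handled or on any target for the other endpoints. It is an error in a stated design property, and it does not show that Phase 2 as a whole is too small.

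**What to change.** In the sample-size paragraph, give the expected 95% half-width for 90% sensitivity as about 6.6 points per site (80 cases) and about 3.3 points pooled (320 cases). Confine the 5% precision claim to the overall analysis.

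Two additions would help but are optional:
- Give the expected half-widths for 70% specificity, about 6.9 points per site and 3.4 overall. Label them as information and note that 170 and 680 non-TB participants are upper limits.
- State whether the 80 is net of Possible TB exclusions. If it is not, give the half-width under a stated loss, for example 6.9 points at an assumed 10%.

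The cost is a few sentences and a less favourable site-level figure. Enrolment, design and analysis do not change.
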